**Fig 4 pone.0331290.g004:**
[figure not shown]
Iterative model optimisation process.

### Implementation framework to guide the development and optimization of the model

We will use the consolidated framework for implementation research (CFIR) to examine complex health interventions, combining theoretical constructs and an active change process that is adaptable for emergency care systems (ECS) (Fig 5). It ensures that interventions are contextually relevant, addressing various facets of ECS through five distinct domains: outer settings, inner setting, individuals involved, intervention characteristics, and the process of implementation. The determinant framework used for implementing high quality ECS in this study is described in S2 Table. Within these domains lie 48 constructs, each capable of acting as a barrier or facilitator to implementation [15,17]. The flexibility and inclusiveness of CFIR makes it suitable for participatory action research, systematically assessing elements influencing both implementation and effectiveness.

**Fig 5 pone.0331290.g005:**
[figure not shown]
CFIR framework used for INDIA-EMS model.

### Scaling up of the final model

The piloted final model ‘Px’ will be scaled up step-wise to the entire district in a phased manner. The scaling-up sequence will start from the hub and spoke system where pilot testing was conducted and then progressively moved to the other spokes and other hubs of the district. A detailed scale-up strategy, tools to be used for scale-up and scalability of the model will be co-developed by consultation with the state. The objective during this phase is to implement the final high-quality integrated INDIA-EMS model across the whole district to achieve 80% population coverage of this model. This rollout will be done primarily by the district administration (the implementation team), with support from the program learning team. The outcome assessment team will conduct the concurrent evaluation and the endline population survey.

### Evaluation of the India-EMS model

The primary aim of the study is to develop an optimized model of integrated high-quality emergency care, which will achieve a population coverage of 80% in the district.

#### Primary outcomes.

The primary outcome indicator is coverage (S3 Table), i.e., the proportion of patients who were provided definitive care for the specified emergency medical condition at an appropriate health facility in a time-sensitive manner. The appropriate facility will be defined during the facility mapping for each emergency condition. Time sensitivity will be defined as per disease condition and decided based on expert consultation and available evidence during the formative phase.

I. *Emergency health care coverage indicators that would be covered are:*a) Proportion of patients who sought care for any emergency medical conditionb) Proportion of patients who used ambulance services to reach health facility for a emergency medical conditionc) Proportion of times an ambulance responded to the emergency calls.d) Proportion of patients who were provided definitive care for the specified emergency medical conditione) Proportion of patients who utilized PMJAY/state government insurance schemes during care for emergency medical conditionsf) Proportion of patients who had catastrophic expenditure during care for emergency medical conditions

The coverage indicator will be disaggregated for different emergency conditions

The second indicator which will be assessed is preparedness of the emergency health care.

II. *Emergency health care preparedness indicators*a) Proportion of health facilities having a fully equipped functional ambulanceb) Proportion of ambulance personnel trained in “at scene and transit” management of common emergenciesc) Proportion of lay first responders trained in “at scene” management of common emergenciesd) Proportion of health facilities having round-the-clock availability of complete emergency care team trained in management of medical emergencies/trauma/poisoninge) Percentage health facilities having availability of key/essential equipment and medications required to provide definitive care for specified emergency conditionf) Percentage health facilities having an infrastructure readiness score above a desirable levelg) Proportion of health facilities providing care as per Standard Treatment Workflow (STW) and Standard Operating Procedure (SOP) as per the level of care for the management of emergency medical conditionh) Proportion of health facilities conducting regular mortality audits of emergency medical conditioni) Proportion of health facilities utilizing RKS funds for emergency care

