Evaluation will be done at baseline, concurrently during the implementation of the model and at the endline(S5 Table). Baseline, concurrent evaluations, and end-line survey data will be analysed to assess the feasibility, acceptability and the cost of the implementation of the model, and the effectiveness of the implemented model in terms of emergency care preparedness and coverage. Concurrent evaluation: Health facility assessment, qualitative interview with stakeholders, competency assessment of care providers will be done concurrently at an interval of three months. Post-care interviews (telephonically) of patients will be done to assess coverage and timeliness of care, expenditure, pathway of care, and delay in care. Endline evaluation: Endline survey will be conducted after the completion of the implementation phase. The sampling strategy and methodology of the endline survey will be similar to the baseline survey. Objective of the endline survey will be to estimate the increase in population coverage and health facility preparedness as compared to the baseline. The estimate of population coverage (i.e., reaching the appropriate health facility within a specified time frame as per the condition; this time frame will be decided during the formative research) obtained during the baseline survey will be used to calculate the sample size for the endline survey. Thus, the sample size for the endline survey will be calculated after the analysis of the results of the baseline survey. We are providing an illustration for sample size required for different scenarios of population coverage assuming a power of 80%, the confidence level of 95%, and a non-response rate of 20%. Thus, sample size included in baseline survey (at the district level) will be sufficient if there is at least 20% increase in population coverage from pre-intervention to post-intervention.

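### Coverage, the primary outcome, has two conflicting definitions: timely definitive care, or timely arrival at the facility. The 80% target does not say which applies, and the endline is to be sized on arrival.

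*Protocol article*

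**What the plan says.** **Primary outcomes.** Coverage is named as the primary outcome indicator and defined as "the proportion of patients who were provided definitive care for the specified emergency medical condition at an appropriate health facility in a time-sensitive manner". On the time limit: "Time sensitivity will be defined as per disease condition and decided based on expert consultation and available evidence during the formative phase". Six coverage indicators, (a) to (f), follow. Indicator (d) mentions definitive care without a facility or time condition.

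**Endline evaluation (closing paragraph under Secondary outcomes).** The stated objective of the endline survey is to estimate the increase in population coverage and facility preparedness over baseline. Population coverage is explained there as "reaching the appropriate health facility within a specified time frame as per the condition; this time frame will be decided during the formative research". The estimate of this quantity "obtained during the baseline survey will be used to calculate the sample size for the endline survey". Table 2 is offered as an illustration, and the endline size is to be worked out once the baseline results are analysed.

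**The target.** Evaluation of the India-EMS model describes a model "which will achieve a population coverage of 80% in the district". Scaling up of the final model sets the objective "to achieve 80% population coverage of this model". The Aim and objectives section gives the same 80% figure. None of these places says whether coverage means arrival or definitive care.

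**The concern.** Both wordings are offered as definitions of coverage, and nothing in the article reconciles them. They classify some patients differently. Someone who reaches the right facility inside the window but gets no definitive treatment, or gets it too late, is covered by the endline definition and not covered by the primary outcome definition.

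The article itself treats arrival and treatment as different events: its process indicators list time to arrival and time to treatment separately. Its preparedness indicators track round-the-clock trained teams and the equipment and medicines needed for definitive care. Arriving in time without being treated is therefore something the study expects may happen.

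Two things are at stake. The 80% claim could be met under one definition and missed under the other, with the choice still open when the results are known. And the baseline proportion entered into the endline sample-size calculation would not be the proportion named as the primary outcome.

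**Working it through.** **1. The two definitions side by side**

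| Patient | Primary outcomes definition | Endline definition |
|---|---|---|
| Reaches appropriate facility in time, definitive care in time | success | success |
| Reaches it in time, definitive care late or not given | failure | success |
| Reaches it after the arrival limit, definitive care within a longer treatment limit | success | failure |
| Neither in time | failure | failure |

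The third row exists only if the arrival limit is shorter than the treatment limit. Both limits are left to the formative phase. With one common window the third row is empty, because timely care at the facility implies timely arrival there. The arrival proportion is then at least as high as the care proportion.

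**2. Size of the gap at the target**

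With a common window, let q be the share of timely arrivals who receive timely definitive care:

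coverage by definitive care = coverage by arrival × q

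The documents do not give q. The range 0.6 to 0.9 is an assumption.

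- q = 0.9: 0.80 × 0.9 = 0.72
- q = 0.8: 0.80 × 0.8 = 0.64
- q = 0.6: 0.80 × 0.6 = 0.48

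**3. Reproducing Table 2**

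Inputs from the endline paragraph: 80% power and 95% confidence (two-sided 5% assumed, since sidedness is not stated). For two independent, equal-sized samples, with unpooled variance and a continuity correction, d = p2 − p1:

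n = (1.960 + 0.842)² × [p1(1 − p1) + p2(1 − p2)] / d²

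n_c = (n/4) × [1 + √(1 + 4/(n·d))]², rounded up

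- 20% to 40%: n = 7.849 × 0.40 / 0.04 = 78.5; n_c = 88.2, so 89 (Table 2: 89)
- 30% to 50%: n_c = 100.01, so 101 (Table 2: 101)
- 40% to 60%: n_c = 103.95, so 104 (Table 2: 104)

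All 13 case numbers in the table reproduce this way. The formula is not at fault here. The question is which proportion goes into it.

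**4. Cases needed for definitive care when q is the same at both surveys**

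| Arrival | q | Definitive care | Cases needed | Table 2 |
|---|---|---|---|---|
| 20% to 40% | 0.9 | 18% to 36% | 103 | 89 |
| 20% to 40% | 0.6 | 12% to 24% | 174 | 89 |
| 40% to 60% | 0.9 | 36% to 54% | 127 | 104 |
| 40% to 60% | 0.6 | 24% to 36% | 242 | 104 |

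At the Table 2 case numbers, power for definitive care (normal approximation, no continuity correction) would be about 0.78 to 0.55 in the first scenario and 0.75 to 0.47 in the second.

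**5. Cases needed when the model also raises q**

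| Arrival | q, baseline to endline | Definitive care | Cases needed | Table 2 |
|---|---|---|---|---|
| 20% to 40% | 0.6 to 0.75 | 12% to 30% | 88 | 89 |
| 20% to 40% | 0.6 to 0.9 | 12% to 36% | 54 | 89 |
| 40% to 60% | 0.6 to 0.75 | 24% to 45% | 86 | 104 |
| 40% to 60% | 0.6 to 0.9 | 24% to 54% | 44 | 104 |

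Sizing on arrival is too small in step 4 and large enough in step 5. The direction depends on a share that the documents do not give.

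**The case against.** Several points on the other side are sound and limit what can be claimed.

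- **Arrival is not always the higher figure.** That needs a common time window, which the article does not fix. This stands, and the 48–72% figure is conditional on it.
- **Nothing has been sized wrongly yet.** The endline size is to be calculated after the baseline, and Table 2 is a grid that serves whichever proportion is entered. This also stands. It means that the correction is still timely; the conflict in the text remains.
- **Power may not suffer.** A reader might infer that sizing on arrival leaves the endline underpowered. The documents do not support that. The model is meant to improve care inside facilities, so q may well rise, and step 5 shows that the arrival-based number can then be more than enough.
- **Other wordings are weak evidence.** A reader might count indicator (d) and the scale-up section's reference to coverage of the model as third and fourth definitions. Indicator (d) is one of six component indicators and may simply be an abbreviated label, with detail in S3 Table, which is not shown. The scale-up wording can be read as a roll-out objective. The point does not rest on either.
- **The fix may not be wording alone.** The household survey is described as covering care sought, pathways, delay in seeking care, expenditure and insurance. Neither that description nor the data collection section names receipt or timing of definitive care. This stands and is carried into the fix.

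None of this reconciles the two definitions. S3 Table may detail the indicator, but it would not remove the conflict between the two statements in the main text.

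**Conclusion.** The primary outcome is wrong as written, because the article defines it twice with different content. The arrival definition is the one tied to endline sizing, and the 80% target does not say which definition it uses. Since the article states both definitions, this is a contradiction and not detail left to a fuller document.

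The size depends on two assumptions: one common time window, and 60–90% of timely arrivals receiving timely definitive care. Under these, 80% by arrival is 48–72% by definitive care, a shortfall of 8 to 32 percentage points against the target. The effect on endline power has no settled direction. If the share stays constant, the case numbers needed are roughly 16% to 133% above Table 2 in the two scenarios worked (103/89 = 1.16; 242/104 = 2.33). If the share rises enough, they fall below Table 2. The ambiguity over the 80% claim remains in either case.

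**What to change.** Before the endline is sized, use the Primary outcomes definition (definitive care, at an appropriate facility, within the condition's time limit) in all of these places:

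1. the endline evaluation paragraph, replacing the explanation in terms of arrival;
2. the baseline estimate that enters the endline sample-size calculation;
3. the baseline-to-endline comparison;
4. the 80% target, wherever it is stated.

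Use the same denominator at both surveys. Report timely arrival at the appropriate facility as a separate secondary step.

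**Cost.** The text change is small. The sponsor must also confirm that the baseline and endline surveys record receipt and timing of definitive care. The study began in January 2024, so the baseline instrument may already have been used. If the baseline did not record these items, the protocol should state that the baseline-to-endline comparison and the 80% claim refer to timely arrival only.

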#### Secondary outcomes.

The secondary outcome of the study will be Implementation outcome and process outcome indicators.

*Implementation outcome:* Implementation of the model will be assessed for following three parameters; acceptability (patient satisfaction and acceptability of health care workers), cost (cost incurred by the health system and project team in implementation of the model), and feasibility (challenges faced during the implementation, adoption of the model and program learning). During the scaling-up phase following implementation outcomes will be captured.

*Process outcome indicators:* These indicators will be used during formative research for optimising the model (S4 Table). These will feed into the codesign workshops, which will help refine the model every 3 months and lead on to building the final Px Model. They include time to arrival and time to treatment for selected emergency conditions. These will be measured by the program support team every three months for 24 hours by live observations. They will also be modified and adapted during the formative research phase.

Evaluation will be done at baseline, concurrently during the implementation of the model and at the endline(S5 Table). Baseline, concurrent evaluations, and end-line survey data will be analysed to assess the feasibility, acceptability and the cost of the implementation of the model, and the effectiveness of the implemented model in terms of emergency care preparedness and coverage. Concurrent evaluation: Health facility assessment, qualitative interview with stakeholders, competency assessment of care providers will be done concurrently at an interval of three months. Post-care interviews (telephonically) of patients will be done to assess coverage and timeliness of care, expenditure, pathway of care, and delay in care. Endline evaluation: Endline survey will be conducted after the completion of the implementation phase. The sampling strategy and methodology of the endline survey will be similar to the baseline survey. Objective of the endline survey will be to estimate the increase in population coverage and health facility preparedness as compared to the baseline. The estimate of population coverage (i.e., reaching the appropriate health facility within a specified time frame as per the condition; this time frame will be decided during the formative research) obtained during the baseline survey will be used to calculate the sample size for the endline survey. Thus, the sample size for the endline survey will be calculated after the analysis of the results of the baseline survey. We are providing an illustration for sample size required for different scenarios of population coverage assuming a power of 80%, the confidence level of 95%, and a non-response rate of 20%. Thus, sample size included in baseline survey (at the district level) will be sufficient if there is at least 20% increase in population coverage from pre-intervention to post-intervention.

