### Model optimization and development phase

Pilot testing of the model (M0) will be done in a limited sample and geographical setting which is likely to be representative of the entire district in consultation with the state. A single hub and spoke cluster will be chosen to have a representation of each level of health facility (prehospital care, Level 1, Level 2, Level 3, and Level 4) for each of the emergency conditions. Pre- and post-implementation data will be analysed to assess acceptability, feasibility and effectiveness based on process and quality outcome measures. Quantitative data on key indicators on the implementation strategy (e.g., effectiveness of training of care providers, appropriateness and effectiveness of educational materials), process indicators (e.g., adherence to new care protocols, patient satisfaction), and implementation measures (e.g., acceptability by the care providers) will be collected. The model will be refined based on a review of the provisional model, data collection and evaluation of the key indicators. As described in the formative research multi-stakeholder consultation (Co-design workshop), in-depth interviews and focus group discussions will be done to get further insights. Key areas will be identified where the provisional model has not worked effectively. Necessary adjustments will be made to the model in a consultative manner. Subsequent cycles will be developed by re-iterating the same process. A total of 3 iterative processes will be done to refine the model and to develop the final model (Px) (Fig 4). Each disease process will be deployed sequentially, and iterative processes and periods will be conducted accordingly. The threshold for initiating the scale-up phase will be decided during the formative research phase after the baseline surveys and mapping by the research team. The threshold will be multidimensional and the irrespective of attaining the threshold after 3 iterative cycles scale up will be initiated.

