### Data collection instruments

Community survey and health care provider/stakeholder survey will be done using a structured questionnaire to capture the occurrence of an emergency medical condition in the last 12 months and treatment seeking behaviour, and barriers and facilitators in seeking care. We will also capture the electronic health record data for disease burden, care and outcome related information. Competency of health care providers will be assessed using knowledge and skill observation checklist. Gap analysis of the health facilities will be done using a structured questionnaire which will be developed during formative research based on review of literature and expert consultation.

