### Data management

Data management will involve the use of a paperless data collection tool and will include geo-spatial tagging and analysis (using space-time matrix and kernel density), development of a Health Management Information System (HMIS) which includes registers, reports, and databases, real-time supportive supervision, interim analysis for process indicators through serial analysis, internal checks for data validation, text mining for qualitative data, and an iterative “inductive” framework analysis. The digital tools and the platform will be developed along with the ICMR HQ and the Gujarat team. The data servers and management will be hosted at ICMR. The qualitative data from FDG, IDI’s and semi-structured interviews will be transcribed and translated at the study site and analysed. The quantitative data management will be done at the respective study site.

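### A 24-hour observation window once a quarter is too thin for condition-specific arrival and treatment times to guide model refinement or show a process gain

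*Protocol article*

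**What the plan says.** Under Secondary outcomes, the article describes a set of process outcome indicators used to optimise the model. On their content: "They include time to arrival and time to treatment for selected emergency conditions". On their use: "These will feed into the codesign workshops, which will help refine the model every 3 months and lead on to building the final Px Model". On their measurement: "These will be measured by the program support team every three months for 24 hours by live observations". It adds: "They will also be modified and adapted during the formative research phase".

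The section Model optimization and development phase places the cycles in one hub-and-spoke cluster that must contain every facility level. It allows three cycles, introduces the conditions one after another, and states: "Pre- and post-implementation data will be analysed to assess acceptability, feasibility and effectiveness based on process and quality outcome measures".

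Two other sections describe data that run beyond the observation day. Data collection instruments says: "We will also capture the electronic health record data for disease burden, care and outcome related information". Data management plans the "development of a Health Management Information System (HMIS) which includes registers, reports, and databases". Neither section is linked to the arrival and treatment times.

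The main text gives no catchment population for the pilot cluster, no number of facilities observed per round, and no minimum number of observed cases.

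**The concern.** Timeliness is central to this model: the primary outcome itself requires definitive care within a condition-specific time limit. Arrival and treatment times are the process measures closest to that outcome, and the article uses them to steer the revisions.

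Because conditions are introduced in sequence, the count that matters is the number of cases of one condition in one cluster in one round. If that count is a handful or fewer, a difference between successive rounds cannot be told apart from chance. A single day also cannot average out day-to-day variation in caseload, staffing or traffic. The workshops could then act on an apparent improvement or failure that is noise, and the final model could go to scale with no demonstrable gain in these times for most conditions.

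**Working it through.** **Inputs from the article**
- Burden of all target emergencies together: 141 per 10,000 (Formative research). It is read as annual because the survey asks about the last 12 months (Data collection instruments).
- Conditions: eight (Study population and sites).
- Window: 24 hours every three months (Secondary outcomes).
- Site: one hub-and-spoke cluster (Model optimization and development phase).

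**Assumptions, since the article gives no figures**
- Pilot catchment of 100,000, 500,000 or 1,000,000.
- Cases spread equally over the eight conditions.
- Every case reaches an observed facility. This is generous, because some patients never reach care.

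**Step 1. The article's own figure.** No case count is stated for the observation rounds. The figure that uses the 141 per 10,000 is the survey sample size: n = z²(1 − p)/(p·e²), with p = 0.0141, e = 0.25, z = 1.96. This gives 3.8416 × 0.9859/(0.0141 × 0.0625) = 4,298, against 4,292 stated. Dividing 4,292 by 0.80 gives the stated 5,365. The burden is therefore being used as intended.

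**Step 2. Share of the quarter observed.** 1/91.3 = 1.1%.

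**Step 3. Expected cases per 24-hour round.** All conditions: catchment × 0.0141/365.25. Average condition: divide by 8. Poisson chance of seeing none: exp(−mean).

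| Assumed catchment | All conditions | Average condition | Chance of no case |
|---|---|---|---|
| 100,000 | 3.9 | 0.48 | 62% |
| 500,000 | 19.3 | 2.4 | 9% |
| 1,000,000 | 38.6 | 4.8 | 0.8% |

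Conditions rarer than average give fewer cases, and commoner ones more.

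**Step 4. What such counts can detect.** For a difference in means between two rounds with n cases each, two-sided 5% and 80% power, the detectable shift in SD units is (1.96 + 0.84) × √(2/n).
- n = 2: 2.8 × 1.000 = 2.8 SD
- n = 5: 2.8 × 0.632 = 1.8 SD
- n = 10: 2.8 × 0.447 = 1.25 SD

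The normal approximation flatters the smallest counts. Ten cases of an average condition per round would need a catchment of about 2 million (9.65 expected).

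**Step 5. The same cluster observed for the whole quarter.** At 100,000 people: 100,000 × 0.0141/4 = 352 cases, or 44 per average condition, about 91 times the one-day count. The detectable shift falls to 2.8 × √(2/44) = 0.60 SD. At 500,000 people it is about 220 per condition and 2.8 × √(2/220) = 0.27 SD. These assume complete capture, so they are upper limits on what continuous recording would give.

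**Sensitivity to the burden figure.** The population column of Table 2 reproduces with 133 per 10,000 (216/0.0133 = 16,241) and not 141. Using 133 would lower the one-day counts by about 6% and leave the conclusion unchanged.

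**The case against.** The best case for the plan has four parts.

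**Other inputs.** The cycles also draw on training effectiveness, protocol adherence, patient satisfaction, provider acceptability, workshops, interviews and focus groups, with facility and competency assessments every three months. A reader might infer that the three cycles rest on chance, or that the observed times decide what is changed. The documents do not support that: they say only that the indicators feed workshops that help refine the model. This part stands in full.

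**Other sources on timeliness.** Telephone interviews after care are to cover timeliness and delay, and Data management mentions serial interim analysis of process indicators. So it would be wrong to say that timeliness is captured only on the observation day. But the interviews are patient reports within the concurrent evaluation, the serial analysis is not said to use recorded times, and the article assigns the process times to live observation.

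**Unknown catchment and case mix.** A reader might infer that most conditions would yield almost no cases. That follows at 100,000 people but not at 1,000,000, where an average condition gives about 5. The times also concern selected conditions, which may be the commoner ones. This stands as a limit on the size of the problem. It does not remove it, because 5 or even 10 cases remain imprecise, and choosing fewer conditions adds no cases to those chosen.

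**Provisional indicators and unseen tables.** The indicators may be adapted in the formative phase, and the supplementary table that lists them is not shown; it may hold operational detail. But the sentence on adaptation commits to no longer window and no case minimum, and the main text states the schedule outright.

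**Conclusion.** The point holds for the condition-specific time indicators and not for the refinement process as a whole. As specified, one round in one cluster gives about 0.5 to 5 cases of an average condition over assumed catchments of 100,000 to 1,000,000. Only very large shifts, about 1.8 SD even with 5 cases per round, could be distinguished from noise. These times are therefore too imprecise to guide a revision by condition or to show a process gain.

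The result rests on an annual reading of 141 per 10,000, equal shares across eight conditions, full arrival at observed facilities, and a catchment that the article does not state. A much larger catchment or a commoner condition would ease the problem.

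The consequence is bounded. These are secondary, formative measures. Coverage and preparedness are assessed from separate data, and scale-up starts after three cycles whether or not its threshold is reached, so noisy times neither bias the primary outcome nor hold up scale-up. What is at risk is a named secondary outcome and the timing evidence available to correct the model before it goes district-wide.

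**What to change.** Reword the process-indicator paragraph under Secondary outcomes so that:

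- arrival and treatment times are taken for all eligible cases of the selected conditions in the pilot cluster over each three-month cycle, from the electronic records and HMIS registers already planned;
- the post-care telephone interviews supplement these times;
- the quarterly 24-hour live observation is kept to check the accuracy and completeness of the recorded times.

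The cost is a change of wording and routine extraction of time stamps from systems the study already intends to use. The downside is that recorded times may be less exact than observed ones, or missing. The retained observation days can quantify both.
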